## Discussion

3

The study describes the protocol for a prospective cohort, single-center study which aims to study the correlation between coronary plaque eccentricity, lesion vulnerability, and 24-months MACE rates in patients with suspected coronary artery disease referred for CCTA for coronary luminal evaluation.

The main contribution of this study is to incorporate the evaluation of coronary plaque eccentricity in routine analysis during coronary computed tomography angiography in order to identify lesions with a more vulnerable phenotype using a noninvasive method.

In this study we hypothesize that lesion geometry has an impact on plaque vulnerability and could be associated with several well-established vulnerability features such as SC, LAP, presence of non-calcified plaques, and lipid-rich atheroma.

Previous postmortem studies demonstrated that plaque rupture and erosion occur more frequently in eccentric atheroma and launched the hypothesis of plaque eccentricity as a feature significantly associated with plaque vulnerability.^[16]^ Costopoulos et al^[17]^ recently demonstrated that plaque rupture occurs in the regions exposed to increased plaque structural stress, which is determined by plaque composition, architecture, and geometry. In their study, the authors reported that plaque structural stress increases with lumen eccentricity (*r* = 0.32, *P* = .001). It has been suggested that hemodynamic forces acting on vascular endothelium can initiate the atherosclerotic process and a pro-atherogenic shear stress profile can be associated with distinct transformation of plaque phenotype toward increased vulnerability.^[18–20]^ At the same time, endothelial shear stress is directly associated with plaque geometry, a baseline low endothelial shear stress being an independent predictor of substantially increasing plaque eccentricity in the study of Papafaklis et al^[21]^ (odds ratio [OR] = 2.33, *P* = .003) and in the study of Puri et al.^[22]^ This shows a complex inter-relation between plaque geometry, hemodynamic profile, and plaque vulnerability.

However, to the best of our knowledge, GEOMETRY will be the first CT-based study investigating a potential direct association between plaque geometry and vulnerability features. Our hypothesis is that plaque eccentricity, exposing the atheroma to an increased circumferential stress, may be responsible for plaque rupture.

Various recent studies reported the role of CT-derived features for characterization of the functional significance of a coronary plaque.^[23,24]^ A recent study published by Kang et al^[15]^ demonstrated that coronary lesion geometry has a direct impact on the functional significance of a coronary stenosis, showing that complex coronary lesions are independently associated with reduced fractional flow reserve (FFR) values and that lesion eccentricity is the most significant independent predictor for low FFR. In the GEOMETRY study presented here, we extended this hypothesis to investigate for the first time the impact of lesion geometry on plaque vulnerability and the association between geometric distribution of atheromatous plaques and the related risk of future cardiovascular events.

## Conclusions

4

In conclusion, GEOMETRY will be the first CCTA-based study that will investigate the impact of geometric distribution of coronary atheromatous plaque on the future risk of cardiovascular events and on the rate of plaque progression, introducing and validating a new potential feature of plaque vulnerability represented by plaque geometry.

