### Background and rationale

1.1

Ischemic heart disease represents the leading cause of mortality worldwide, causing 9.4 million of deaths in 2016.^[1]^ Atherosclerosis represents the underlying condition leading to myocardial ischemia, ultimately resulting in acute coronary syndromes (ACS) and having devastating consequences on public health. The vast majority of ACSs are the consequence of a sudden modification in coronary plaque morphology leading to plaque rupture or erosion, the 2 principal mechanisms triggering an acute coronary event.^[2]^ Atheromatous plaques that are prone to rupture or erosion following a complex process of transformation and alteration of plaque composition are known as vulnerable coronary plaques and can be easily identified nowadays with the help of modern imaging techniques.^[3,4]^ Due to the recent progress in the field of coronary computed tomography angiography (CCTA), it has emerged as a valuable noninvasive imaging tool for assessing atheromatous plaque morphology and composition. Moreover, CCTA-based imaging-derived markers associated with vulnerability have been validated as reliable indicators of the plaque-associated risk. Such key CCTA features of plaque vulnerability identified by previous studies include positive remodeling (PR), low-attenuation plaque (LAP), napkin-ring sign (NRS), and spotty calcifications (SC).^[5,6]^ Interestingly, intravascular ultrasound studies demonstrated that ruptured coronary plaques are usually eccentric.^[7]^ A combined intravascular ultrasound (IVUS) and optical coherence tomography (OCT)-based study reported that lesions demonstrating plaque erosion had a greater plaque eccentricity index than those with plaque rupture or calcified nodules (*P* < .001 and *P* < .001).^[8]^ At the same time, progression of atherosclerotic lesions was more frequent in eccentric lesions than in concentric ones.^[7,9]^ However, the role of lesion eccentricity as a CCTA feature of plaque vulnerability has not been investigated so far. Furthermore, the impact of lesion geometry, as defined by the type of eccentricity (transversal or longitudinal), on the degree of vulnerability is unclear.

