### Study objectives

1.2

The primary objective of the study is to evaluate the association between different patterns of plaque geometry and the risk for major adverse cardiac events MACE (defined as all-cause mortality, cardiovascular death, myocardial infarction, repeated revascularization, repeated hospitalizations for cardiovascular related incidents, cerebrovascular events) during a 2-year follow-up.

The secondary objective of the study is to evaluate the association of plaque eccentricity with plaque vulnerability and plaque progression after 2 years of follow-up.

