### Study design

2.1

GEOMETRY is a prospective, non-randomized, cohort, single-center study to investigate the relationship between plaque eccentricity, plaque vulnerability, and the risk for MACE in order to validate plaque eccentricity as a new CCTA marker of coronary plaque vulnerability.

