### Outcomes

2.8

The primary outcome of the study is represented by the rate of MACE during follow-up. Secondary outcome refers to coronary plaque vulnerability associated to plaque eccentricity, based on the number of vulnerability markers in eccentric versus concentric plaques.

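### The plan aims to validate eccentricity as a new marker, but its outcomes and tests can show only a crude association with MACE, not information beyond the established plaque features

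*Protocol article*

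**What the plan says.** Section 2.1 says the study is done "in order to validate plaque eccentricity as a new CCTA marker of coronary plaque vulnerability", and the last paragraph of Section 1.1 repeats this. Section 4 describes the study as "introducing and validating a new potential feature of plaque vulnerability represented by plaque geometry".

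Section 1.1 treats other CCTA vulnerability markers as already validated. It names four key features: low-attenuation plaque (LAP), positive remodelling (PR), spotty calcification (SC) and the napkin-ring sign (NRS). The Discussion hypothesises that geometry "could be associated with several well-established vulnerability features such as SC, LAP, presence of non-calcified plaques, and lipid-rich atheroma".

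The primary objective in Section 1.2 is narrower than the validation aim. It is to "evaluate the association between different patterns of plaque geometry and the risk for major adverse cardiac events". In Section 2.8 the primary outcome is the MACE rate, and the secondary outcome is vulnerability "based on the number of vulnerability markers in eccentric versus concentric plaques". Section 2.10 sizes the study for a difference between two crude proportions. Section 2.11 names the t test, the Mann–Whitney test and the Fisher exact test. Section 2.6.2 has the four markers and the severity of stenosis read on the CCTA.

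**The concern.** Calling a feature a new marker, where others are already accepted and read on the same scan, invites the question of what it adds to them. Neither stated outcome addresses this. The primary outcome relates eccentricity to MACE, and the secondary relates eccentricity to the established markers. No objective, outcome or named test relates eccentricity to MACE given those markers.

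The protocol's own hypothesis makes this matter. If eccentric plaques carry more established markers, and those markers predict events, the eccentric group may have more MACE even if eccentricity contributes nothing itself. Success on both outcomes would then fit a new marker and a proxy for known ones equally well. This would remain true if the two groups had equal numbers of plaques. At stake is whether the headline conclusion can be drawn from the results.

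**Working it through.** **Reproducing the plan's figure.** Section 2.10 gives 500 per group, MACE-free proportions of 0.90 and 0.90 + 0.054 = 0.954, and two-sided alpha of 0.05. The mean proportion is 0.927.

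- Standard error under the null: √(2 × 0.927 × 0.073 / 500) = 0.01645.
- Standard error under the alternative: √((0.90 × 0.10 + 0.954 × 0.046) / 500) = 0.01636.
- Power: Φ((0.054 − 1.96 × 0.01645) / 0.01636) = Φ(1.329) = 0.908, against the stated 90%. For exactly 90% power, 486 per group are needed.

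The figure reproduces, which confirms that the powered test is the unadjusted contrast of two proportions. These proportions imply 500 × 0.10 + 500 × 0.046 = 73 events.

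**What a proxy would produce.** The article gives no marker prevalence and no marker-specific risk, so the inputs below are assumptions. A patient either carries an established marker or does not. Two-year MACE risk is 4% without it and 4% × RR with it. Eccentricity has no effect once the marker is known. With marker prevalence h in a group, MACE = 0.04 × (1 − h + h × RR). The last column is the exact probability that a two-sided Fisher test at 5% rejects with 500 per group.

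| Marker prevalence, eccentric vs not | RR | MACE, eccentric vs not | Expected events | Fisher significant |
|---|---|---|---|---|
| 20% vs 20% | 5 | 7.2% vs 7.2% | 72 | 3.8% |
| 30% vs 20% | 3 | 6.4% vs 5.6% | 60 | 6.4% |
| 40% vs 20% | 2 | 5.6% vs 4.8% | 52 | 6.7% |
| 40% vs 20% | 3 | 7.2% vs 5.6% | 64 | 14.7% |
| 50% vs 20% | 3 | 8.0% vs 5.6% | 68 | 28.3% |
| 50% vs 20% | 5 | 12.0% vs 7.2% | 96 | 70.2% |
| 60% vs 20% | 5 | 13.6% vs 7.2% | 104 | 90.1% |

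Example, last row: 0.04 × (0.4 + 0.6 × 5) = 0.136 and 0.04 × (0.8 + 0.2 × 5) = 0.072. The first row shows that with equal prevalence the excess disappears, so in this model it comes only from the overlap between eccentricity and the marker.

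**Crude against adjusted.** A second set of assumptions was simulated, with 1,000 trials per row, 500 per group and again no effect of eccentricity itself. The adjusted test is a logistic model with eccentricity and the marker.

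| Prevalence | MACE with / without marker | Group MACE | Fisher significant | Adjusted significant |
|---|---|---|---|---|
| 40% vs 40% | 20% / 5% | 11.0% vs 11.0% | 4% | 5% |
| 50% vs 30% | 20% / 5% | 12.5% vs 9.5% | 31% | 6% |
| 60% vs 20% | 20% / 5% | 14.0% vs 8.0% | 85% | 5% |
| 60% vs 25% | 22% / 6% | 15.6% vs 10.0% | 72% | 7% |

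The adjusted test stays near 5% throughout, while the crude test does not.

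**What an adjusted test could detect.** In a simplified simulation (one marker, 50% vs 20%, marker odds ratio 3, 4% base risk, about 75 to 96 events), a likelihood-ratio test found a true odds ratio for eccentricity of 1.3 in about 16% of trials, 1.5 in about 34% and 2.0 in about 85%.

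**The case against.** **The documents never promise an incremental predictor.** The primary objective asks for an association, and novelty can be read as the first study of this feature on CCTA. Association with known features and with events is a recognised form of validation. This stands in part. A reader might infer that a positive primary result would be worthless, and the documents do not support that, because it would answer the primary objective. But Sections 1.1 and 2.1 use the word validate without the qualifier that Section 4 carries, alongside markers described as already validated.

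**The markers may lie on the causal path.** The Discussion says that "lesion geometry has an impact on plaque vulnerability and could be associated with several well-established vulnerability features" and proposes circumferential stress as a route to rupture. Conditioning on composition could then remove part of a real effect. This stands. A reader might infer that the stronger the secondary result, the less the primary result says about eccentricity. That holds only if eccentricity is a proxy, and the protocol hypothesises a pathway.

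**An excess of MACE is not automatic.** The secondary outcome counts markers per plaque, whereas groups and MACE are defined per patient. The composite also includes all-cause death, cerebrovascular events and cardiovascular rehospitalisation, so a five-fold marker effect on it is a strong assumption. This stands: milder inputs give 6% to 28%.

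**An analysis plan may carry the adjusted model.** It may, and nothing in the design prevents one. The finding is therefore not that a model is missing, but that the stated aim and conclusion reach further than the stated outcomes.

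**Conclusion.** The point holds as a mismatch between the aim and the outcomes. Followed as written, the plan can establish that eccentricity is associated with MACE and with established markers. It cannot separate a marker that adds information from one that stands in for LAP, PR, SC and NRS.

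The size is uncertain. With no effect of eccentricity itself, the crude test is significant in about 6% to 90% of trials when marker prevalence is 30–60% vs 20% of patients, the marker risk ratio is 2 to 5 and the base risk is 4%. All these inputs are assumed. The upper end needs both a large prevalence gap and a five-fold risk. A reader might take 70% or 90% as the expected rate of a misleading result, and the documents give no basis for that. What does not depend on the inputs is that neither stated outcome conditions on the markers.

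**What to change.** Keep the crude MACE comparison as the primary analysis. Add to Section 2.8 one pre-specified secondary analysis of 2-year MACE: a model with PR, LAP, NRS, SC and maximum stenosis, compared with the same model plus eccentricity. Define each marker per patient, because MACE is a patient-level outcome. Report the adjusted effect of eccentricity with its confidence interval and the optimism-corrected change in C-index. State beforehand that the markers may partly mediate the effect, so a null adjusted result does not rule out a role for geometry.

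In the Abstract's conclusion and Section 4, limit the claim to association with MACE unless the adjusted estimate supports added predictive value. This should be a judgement on the estimate and its interval, not a pass or fail on one significance test, which would often miss a genuine moderate effect.

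The cost is one further analysis of variables already read on the baseline scan, and a change of wording. The downsides are limited precision with about 100 events or fewer, and a more cautious claim.
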